**Methods/Design:**

The Surgical Techniques, Open versus Minimally invasive gastrectomy After CHemotherapy (STOMACH) study is a randomized, clinical multicenter trial. All adult patients with primary carcinoma of the stomach, in which the tumor is considered surgically resectable (T1-3, N0-1, M0) after neo-adjuvant chemotherapy, are eligible for inclusion and randomization. The primary endpoint is quality of oncological resection, measured by radicality of surgery and number of retrieved lymph nodes. The pathologist is blinded towards patient allocation. Secondary outcomes include patient-reported outcomes measures (PROMs) regarding quality of life, postoperative complications and cost-effectiveness. Based on a non-inferiority model for lymph node yield, with an average lymph node yield of 20, a non-inferiority margin of −4 and a 90% power to detect non-inferiority, a total of 168 patients are to be included.

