### Power of the study

The number of dissected lymph nodes in gastric cancer surgery is an important marker for radicality of surgery and quality of care [22-24]. Therefore the primary outcome in this study is the number of retrieved lymph nodes in laparoscopic surgery compared to an open procedure.

It is anticipated that laparoscopic gastric resection will show similar surgical resection specimen quality [19], based on the results of the Dutch Cancer Registry (NKR). The sample size calculation is set to achieve 90% power to detect non-inferiority using a one-sided, two-sample t-test. With a margin of non-inferiority at −4.0 and a significance level (α) of 0.05, the sample size requires 66 patients to be included per group, with a total sample size of 132 patients. A non-inferiority margin of −4.0 is deemed feasible, since the current average lymph node yield at the VU University Medical Center ((VUmc) Amsterdam) is around 20, meaning a lymph node yield of 16 is acceptable.

Since lymph node yield is of interest in cases of radical resection, further correction is necessary for radicality of surgery. The NKR showed that a radical resection was achieved in 79% of patients, although palliative resection figures are not given separately. After correction for radicality, a total of 168 patients are to be included. In other, similar prospective studies, no loss to follow-up was recorded, therefore we do not take into account a percentage for loss to follow-up [25,26].

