### Data collection and statistics

Data is collected via a secured Internet module and via datasheets on paper. A secured online module has been especially designed for the STOMACH trial, using OpenClinica, version 3.3. © 2015 OpenClinica, LLC. Paper datasheets, such as completed questionnaires, will be sent to the VUmc by mail, where they are kept in a secured room. Data are collected daily until discharge. PROMs are collected preoperatively, five days postoperatively, at three months, six months and one year postoperatively.

One research fellow in the VUmc will monitor the data of all included patients, and maintain regular contact with all participating centers. All required parameters will be collected in an SPSS data file, SPSS version 22, IBM statistics®, Chicago, Illinois, USA . Data analysis will be performed according to the intention-to-treat principle. Continuous variable will be compared with a T-test or Mann-Whitney U as appropriate, and frequencies will be compared with a chi-square or the McNemar analysis as appropriate.

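### The only stated analysis rule for continuous outcomes is not tied to the −4.0 node margin, and leaves a Mann-Whitney test open for the primary endpoint

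*Protocol article*

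**What the plan says.** The Abstract (Methods/Design) sets out the design: "Based on a non-inferiority model for lymph node yield, with an average lymph node yield of 20". Power of the study names the outcome: "Therefore the primary outcome in this study is the number of retrieved lymph nodes in laparoscopic surgery compared to an open procedure". The same section gives the test used for sizing, "The sample size calculation is set to achieve 90% power to detect non-inferiority using a one-sided, two-sample t-test", and its settings: "With a margin of non-inferiority at −4.0 and a significance level (α) of 0.05". It justifies the margin by noting that the current yield at the coordinating centre "is around 20, meaning a lymph node yield of 16 is acceptable".

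The analysis text stands in Data collection and statistics. After naming intention-to-treat as the analysis principle, it says: "Continuous variable will be compared with a T-test or Mann-Whitney U as appropriate". That sentence covers all continuous variables. It does not set the primary endpoint apart, refer back to Power of the study, or mention the margin.

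**The concern.** Power of the study asks whether the mean node count with the minimally invasive approach is less than 4 nodes below the open approach. The analysis rule answers a more general question. A t-test used simply to compare two arms is, by default, a test of no difference. A standard Mann-Whitney U test has equal distributions as its null hypothesis and yields no mean difference to set against −4.0. Because the choice is left to be made "as appropriate", the primary test could also be picked once the data have been seen.

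Non-inferiority on node yield is the trial's main claim, and the article's Background treats it as a precondition for adopting the technique. If the final report followed the analysis sentence literally, that claim could rest on a test that does not address the margin, with an error rate other than the planned 5%.

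**Working it through.** **Inputs.** From Power of the study: margin 4.0 nodes, one-sided alpha 0.05, power 90%, 66 per group, and a 79% radical resection rate leading to 168 in total. Not stated: the SD of node yield. It is treated below as an assumption, with a range of 6 to 12.

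**Step 1: reproduce the plan's own figures.** With a true difference of zero, the normal approximation is n per group = 2 × SD² × (1.645 + 1.282)² / 4². Solving for SD at n = 66 gives SD = 4 × √33 / 2.926 = 7.85. The exact noncentral-t power at 66 per group is 0.901 for SD 7.8. So the stated result, "the sample size requires 66 patients to be included per group, with a total sample size of 132 patients", is consistent with an SD of about 7.8, although it cannot be checked independently. The inflation also reproduces: 66 / 0.79 = 83.5, hence 84 per group and 168 in total. The sample size is not in dispute.

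**Step 2: where the two procedures part.** Take SD 7.8 and 66 per group.

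- SE = 7.8 × √(2/66) = 1.36.
- A two-sided 5% t-test of no difference is non-significant while the observed deficit is below 1.978 × 1.358 = 2.69 nodes.
- The margin test succeeds only while the deficit is below 4 − 1.657 × 1.358 = 1.75 nodes.
- An observed deficit between 1.75 and 2.69 nodes is therefore not significantly different from zero, yet non-inferiority is not shown.

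**Step 3: false-claim rate if non-significance were taken as non-inferiority.** This is the probability that |T| < t(0.975, 2n − 2) when the true difference is −4. T is noncentral t with noncentrality −4 / (SD × √(2/n)).

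| Assumed SD | 66 per arm | 84 per arm |
|---|---|---|
| 6 | 3.3% | 1.0% |
| 7 | 9.7% | 4.3% |
| 7.8 | 16.8% | 8.9% |
| 10 | 37.4% | 26.9% |
| 12 | 52.4% | 42.6% |

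The margin test gives 5.0% in every row. With a Mann-Whitney test in place of the t-test (5,000 simulated trials, normal data, SD 7.8), the rate is about 18% at 66 per arm and 11% at 84 per arm.

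**Step 4: what the margin test delivers.** At SD 7.8 and 66 per arm, comparing the one-sided 95% lower limit with −4.0 has 90.1% power at a true difference of zero and a 5.0% false-claim rate at −4. These are the operating characteristics that Power of the study asks for.

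**The case against.** The strongest reply is that the margin test is already in the article. Power of the study gives the hypothesis, test, sidedness, margin, alpha and outcome. The analysis sentence is a generic closing line that also has to serve length of stay and quality-of-life scores. It lists the t-test first, which is compatible with the sizing test, and it never says two-sided. An exact decision rule is also something a condensed article may leave to the full protocol or analysis plan. All of this stands, and it means that the lack of a confidence limit is not in itself the fault. What remains is a stated rule that covers the primary endpoint as worded and permits a test that does not fit the design. A fuller document would have to override it.

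Several stronger readings are tempting and should not be adopted:

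- A reader might infer that the investigators will read a non-significant p-value as non-inferiority. No section says so, so the rates in the table are conditional on that misreading.
- A reader might infer that the error is always inflated. It is not: at SD 6 with either size, and at SD 7 with 84 per arm, the rate is below 5%. The two largest SDs also sit badly with the plan's own sizing, since the power of the margin test at 66 per arm would then be 74% (SD 10) and 60% (SD 12).
- A reader might infer that the 90% power is lost because a conventional 95% interval would be used. The article proposes no such interval. At SD 7.8, power against −4.0 with one would be 83% at 66 per arm but 91% at 84 per arm.
- A reader might infer that a Mann-Whitney test can never address a margin. Adding 4 to the minimally invasive counts and testing one-sided does so under a location-shift model. The article specifies neither that version nor that assumption.

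**Conclusion.** The point holds as a mismatch between two stated passages. The trial is sized on a mean difference against −4.0, and the analysis rule as worded allows tests that do not evaluate that difference. The consequence is a risk, not an announced error. At the SD implied by the plan's own sample size (about 7.8), taking non-significance for non-inferiority would raise the false-claim rate from 5% to about 17% at 66 per arm and 9% at 84 per arm. Across SD 6 to 12 the range is 3% to 52% and 1% to 43% respectively. These figures assume normal data with equal variances, a true difference of exactly −4, and an SD that the article does not give.

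**What to change.** Add one sentence for the primary endpoint: non-inferiority is concluded if the lower limit of the two-sided 90% confidence interval (one-sided alpha 0.05) for the difference in mean lymph node count, minimally invasive minus open, lies above −4.0. Base the interval on the t distribution (Welch) or a linear model. If the counts are skewed, add a bootstrap interval for the same mean difference as a sensitivity analysis. Limit the existing t-test or Mann-Whitney sentence to the other continuous outcomes, and state that a non-significant difference is not evidence of non-inferiority.

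This keeps the margin, alpha and power already stated. It costs a short wording change, with no extra patients or data, and should be settled before outcome data are examined.

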### Ethics

The study is conducted in accordance with the principles of the Declaration of Helsinki and ‘good clinical practice’ guidelines. The independent medical ethics committee of the VUmc (Medisch Ethische Toetsingscommissie VU Medisch Centrum, Amsterdam, the Netherlands) has approved the final version of the protocol prior to the start of the study (approval number: 2014.354 - NL51293.029.14). Written informed consent will be obtained from all participating patients. This trial was registered on 28 April 2014 at Clinicaltrials.gov with the trial number NCT02130726.

### Surgical technique

#### Preoperative preparation

All patients will receive the same preoperative preparation, regardless of allocated treatment. All participating patients will receive standard preoperative prophylactic antibiotics consisting of a single dose of cefuroxime at 1,500 mg and a single dose of metronidazole at 500 mg. Antithrombotic prophylaxis will be administered according to local protocol.

#### Open gastrectomy

For the open gastrectomy, the patient is placed in the supine position. Access to the abdomen is obtained via a median laparotomy. The Omnitract® system, Omni-tract Surgical, St Pauls, Minnesota, USA, is placed over the incision in order to secure vision over the stomach.

#### Minimally invasive gastrectomy

For the minimally invasive gastrectomy, the patient is placed in the reverse Trendelenburg position and the legs are abducted. The surgeon is positioned between the legs of the patient. The first trocar, for the laparoscope, is inserted at the umbilicus. After insertion, a pneumoperitoneum is created. The following trocars are placed with the aid of the laparoscope. The overview of trocar placement is depicted in Figure 1. A Nathanson Hook Liver Retractor® may be placed in order to retract the liver from the operation area.

**Figure 1 Fig1:**
[figure not shown]
**Overview of placement of trocars in minimally invasive gastrectomy.** 1) laparoscope placement, 2) Nathanson Hook Liver Retractor, (3 and 4) additional instruments, 5) the incision (±5 to 6 cm) is performed in order to allow for retrieval of the specimen, and the wound is protected with an Alexis® wound protector, Applied Medical Resources Corp, Rancho Santa Margarita, California, USA. Dotted line portrays open gastrectomy.

#### Gastrectomy

After the placement of trocars or opening of the abdomen, the abdomen is inspected for signs of tumor progression. The greater omentum is mobilized and dissected from the transverse colon. Access to the lesser sac is obtained. The right gastro-epiploic artery is identified and clipped and according lymph node stations dissected. This is followed by further dissection and ligation of the right gastric artery and harvesting of the hepatic lymph node stations. The duodenum is dissected up to 5 cm distal to the pylorus, followed by transection of the duodenum.

Dissection continues with mobilization of the left part of the stomach. After identification of the left gastric artery, the artery is clipped and according lymph node stations are harvested. Further dissection continues towards the hiatus, where the pericardial lymph nodes are harvested. After the gastro-esophageal junction is identified and dissected, it is transected using a linear stapling device. With regard to transection, a proximal margin of 6 cm from the tumor is recommended [3]. After *en bloc* resection, the specimen is removed, but not yet stored. After completion of the surgery, the surgeon attaches tags with numbers corresponding to each lymph node station, allowing for separate analysis of each lymph node station.

Reconstruction occurs with a Roux and Y anastomosis. First, the jejunum is mobilized upwards in a retrocolic fashion. Anastomosis between the esophagus and jejunum is performed. Next, a jejunojejunostomy is fashioned. A final overview is performed of the abdomen, with control of hemostasis. Lastly, a silicone drain is placed in the operated area, if deemed necessary by the operating surgeon, and the abdomen is closed.

#### Postoperative management

Irrespective of open or minimally invasive gastrectomy, patients will receive similar postoperative management. Depending on local protocol, a nasogastric tube may be positioned. Oral diet is initiated. Postoperative pain control consists of patient-controlled analgesia (PCA), which is monitored daily by an anesthesiologist. PCA pumps will remain *in situ* for a maximum of three days. Patients are encouraged to be out of bed and walking around the ward, under the guidance of a physiotherapist or nurse. Patients will be discharged when they pass stool, are able to drink, can walk and are comfortable with oral analgesia. A delay in discharge due to ‘social’ reasons will be recorded. Follow-up occurs at the outpatient clinic; patients are seen routinely at three, six and 12 months postoperatively.

## Discussion

Laparoscopic surgery has been shown to provide important advantages in comparison with open procedures in surgery of the rectum and colon. Since the first minimally invasive total gastrectomy in 1996 by Azagra *et al*. [29], several comparative studies between open and minimally invasive approaches of the stomach have been published. Short-term results show less perioperative blood loss, faster patient recovery and earlier discharge from the hospital. One study reported long-term results with similar survival and disease-free survival rates in the open and minimally invasive approach [10].

Most studies are conducted in Asian countries, where a screening program has enabled early detection and treatment. The results of these studies cannot be translated to the Western population. Western studies have deemed minimally invasive gastrectomy to be feasible, although the numbers are small and the studies often underpowered. Furthermore, these studies were conducted before the implementation of neo-adjuvant therapy. Currently, in the Netherlands, less than 10% of patients are operated on via a minimally invasive approach [30]. A prospective, randomized clinical trial is considered necessary in order to establish the optimal surgical technique in gastric cancer: open or minimally invasive gastrectomy.

## Trial status

The Scientific Research Committee of the Cancer Centre Amsterdam, NL, approved the design of the STOMACH trial. The Medical Ethical committee of the VUmc has approved the protocol (approval number: 2014.354 - NL51293.029). The trial is open for recruitment since January 2015.

## Abbreviations

ASA: American Society of Anesthesiologist classification
EORTC: European Organisation for Research and Treatment of Cancer questionnaires
EQ-5D: Euro-Qol (Quality of Life)-5D questionnaire
ICU: Intensive care unit
NKR: Nederlandse Kanker Registratie (Dutch Cancer Registry)
PCA: Patient-controlled analgesia
PROMs: Patient-reported outcome measurements
STOMACH: The surgical techniques, open versus minimally invasive gastrectomy after chemotherapy trial
VUmc: VU University Medical Center
